In prior work we have found the following to be particularly significant in the building, maintaining and destruction of rapport: the verbal behaviors called conversational strategies, such as self-disclosure and reference to shared experience, the non-verbal behaviors of eye gaze, head nods, and facial expressions such as smiles, and the paraverbal behaviors of laughter and pitch excurses (large variations in intonation). In each case, reciprocal instances of these behaviors (where both interlocutors engage in the behavior at roughly the same time—laughing together, or disclosing intimate information one after another—and conjunctions of these behaviors across communication modalities (what is called “multimodal communicative behavior”), appear to carry the most weight (see Cassell, 2000; Schegloff, 2007 for a general discussion of conversational behaviors). In such analyses it is essential to require ground truth as to the strength of the psychological state of rapport, so that the behaviors and psychological state are independently assessed. To this end, the level of rapport between two individuals relies on assessment by naive observers, given a general definition of rapport, and using the thin slice technique pioneered by Ambady and Rosenthal (1993). This is in contrast to some recent neuroscience literature where annotators are told to use particular non-verbal behaviors, such as mutual eye gaze or head nods, to rate rapport. It is important to consider that conflating the presence of non-verbal behaviors with social bonds risks circularity in the analysis process.

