Bringing these axes together we predict that we will find stronger and more generalized IBS where conversational behaviors (verbal, non-verbal, and paraverbal) are reciprocal. That is, in cases of mutual eye gaze and mutual smiles, reciprocal self-disclosure, and entrainment (sometimes called alignment) where the pattern of behavior is increasingly similar between members of a dyad, such as increasingly similar speech rate. We predict that these patterns of dyadic behavior will be followed by increased IBS and that, in turn, this will allow us to distinguish between productive and unproductive rapport on the basis of IBS that follows dyadic behavior. That is to say, IBS will be present in more regions of interest, and will be stronger, when it co-occurs with high rapport that accompanies (and just precedes) learning gains.

Here, due to its non-invasive nature, high safety profile, reduced sensitivity to participants' motion, and higher spatial resolution than EEG, the fNIRS technique can play an important role (Providência and Margolis, 2022). Its reduced sensitivity to movement makes it ideally suited to investigate the naturalistic phenomena that make up social interaction (Pinti et al., 2020), and particularly social interaction among children, who may find it difficult to stay completely still. While EEG captures responses to individual events at a high temporal granularity (single syllables, articulation of the face), fNIRS integrates over these to reveal the different brain region that are more or less active on the timescale of seconds, and therefore allows us to focus on overall task components, rather than events at the sensory modality level of resolution.

An earlier study conducted by Rabinowitch and Knafo-Noam (2015) found that ratings of closeness were higher for children who participated in a synchronous finger tapping exercise, a result thought to illustrate the positive effects of synchronous (non-conversational) interaction in children, but given the increased focus in neuroscience on actual social interaction, and the tools available to do so, it is time to study IBS in child dyads engaging in actual social interaction, with an eye toward better understanding and better implementation of supporting technologies.

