For each dyad, we will obtain IBS values for each 30 second epoch and each ROI pair. We will also compute the average IBS across each 8–10 min phase of the experiment. In total, we will thereby obtain IBS values for each dyad, from each ROI, for the entire phase and for each 30-second epoch within that phase. To best capture the IBS evoked by social interaction, we normalize the values of the social phase by computing a Z-score, i.e., removing the average value of the solo phase and dividing by the standard deviation. This process is repeated for each dyad. To compare the difference between phases, then, we run a general linear model (GLM). Normalized IBS values are entered as the dependent variable with interactive phases (i.e., collaboration and discussion) and the interaction effect of ROIs (six per dyad) as fixed factors. To assess whether the observed neural activity is most likely due to exchanges between the children, as opposed to being primarily driven by the content of the task, we will also generate random pairings by calculating IBS with false dyads (the child's time-series paired to the time-series of another child coming from a different dyad during the same phase). We will create multiple such random pairs to generate the distribution of IBS expected under the null hypothesis (H0) (Nguyen et al., 2021a). The values of the actual real pairs will then be compared to these H0 distributions, thus providing an empirical *p*-value. An example of this analysis is illustrated for the feasibility study in Figure 5B. We will also generate a more conservative intra-pair comparison based on temporally shuffled behavior. In this case, the participants stay the same but the epochs are randomized to generate false dyads (Ayrolles et al., 2021).

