### 5.3 Behavioral annotation

We argued above that it is not sufficient to focus on one single conversational behavior, nor one single modality of conversational behaviors, in order to understand the ways in which the behaviors of social interaction are related to IBS. Here we describe how we acquire the multimodal data. Conversation is influenced by the situational context (e.g., classroom vs. playground, brainstorming vs. class presentation), and by the interlocutor (e.g., adult vs. child, stranger vs. friend or family member). These differences underscore the importance of rigorous annotation, including using automatic extraction based on advances in signal processing to allow efficient treatment of large amounts of data, as well as hand annotation using coding manuals tested and normed for the culture and age group in question.

In terms of the automatic extraction of nonverbal behavior, we will employ OpenFace, a widely-used open-source computer vision framework that utilizes action units (AUs) to detect facial landmarks, allowing us to detect facial expressions in video (Baltrusaitis et al., 2018). AUs are translated into behavioral features such as smiles. This allow us, for example, to differentiate between the Duchenne or genuine smile and the polite smile (Ekman et al., 1990). We will next perform a manual check on 10% of the data at each age using the ELAN video annotation tool (Wittenburg et al., 2006) to ensure that the behaviors are correctly annotated by the software. We have conducted such checks in the past, and have found alignment between high inter-rater reliability hand annotation and OpenFace. If, however, this is not the case for these data for any reason, we will fine-tune the software with the annotated data to ensure alignment and then retest on a second sample of 10%. Second order behaviors (e.g., mutual smiles) will then be automatically extracted. Assessment of eye gaze in the videoconference-mediated conversations will be achieved using the framework developed by Tran et al. (2022) applied to the raw eye gaze data generated by OpenFace. This application enables the extraction of eye gaze direction employing a dynamic clustering algorithm. As with facial expression, we will then automatically extract the second-order behavior of mutual eye gaze.

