### 6.1 Claim 1: conjunctions of conversational behaviors across modalities better predict IBS

We argue that focusing on a single conversational behavior (such as eye gaze) under-estimates the complex interplay among modalities in their relationship to neural synchrony. To adduce evidence for this claim we will leverage Long Short-Term Memory (LSTM) networks to predict IBS on the basis of temporal sequences of behavioral data (see Table 1 for further details on the behavior types and variables). Since conversational behaviors are likely to lead to IBS with a certain lapse of time, we insert a 1 to 10 second time lag between the sequences of conversational behaviors and the IBS (Chang et al., 2022). The dataset will be structured into sequential behavioral data over time, each associated with a 30-second interval IBS value and normalized through a Min-Max scaling technique, ensuring consistent proportions across all features, while preserving the original distribution of the data.

**Table 1 T1:** Data sheet.

**Level of data type**	**Modality**	**Dyadic status**	**Specific variables**	**Notes**
Conversational Behavior	Verbal	Non-reciprocal	◾Self-disclosure	Number of behaviors per 30 second epoch.
			◾Reference to shared experience	
			◾Praise	
			◾Teasing	
		Reciprocal	◾Mutual self-disclosure	
			◾Mutual reference to shared experience	
			◾Mutual teasing	
	Paraverbal	Non-reciprocal	◾Pitch shift	
			◾Shift in speed of speaking	
			◾Shift in loudness	
		Reciprocal	◾Mutual pitch shift	
			◾Mutual shift in speech rate	
			◾Mutual shift in loudness	
	Nonverbal	Non-reciprocal	◾Smile	
			◾Head nod	
			◾Gaze at other person	
		Reciprocal	◾Mutual smile	
			◾Mutual head nod	
			◾Mutual eye gaze	
Rapport State		Rapport rating (1–7) for each 30 second interval for each dyad		
Educational Performance		Every week	Task 1–3, week (with x = 1–6)	◾Number of hypotheses per weekly 8–10 min read-out
				◾Number of pieces of evidence per 8–10 min weekly read-out
IBS				◾Right hemisphere ROIs

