### 6.3 Claim 3: IBS Granger-causes reciprocal conversational behaviors

While the previous analyses give a sense of the relationship among time courses, they do not illuminate the direction of influence between one time course and another. To that end, we will compute Granger causality (Granger, 1969). Our prior work already shows that rapport Granger-causes increasing entrainment in some conversational behaviors, and particularly in speech rate (Sinha and Cassell, 2015b). It has also been employed to show that dual brain stimulation improves collaborative learning via the mechanism of spontaneous movement synchrony (Pan et al., 2021). Here we seek to understand whether rapport Granger-causes IBS or vice-versa and, subsequently, whether conversational behaviors Granger-cause IBS or vice-versa. Given the slower time scale of fNIRS signals, a relatively large time window will be used. That is, we hypothesize that it might take as long as 5 seconds for one of these phenomena to Granger-cause the other. The Granger causality approach relies on the accuracy of one time series in predicting the future behavior of another time series. In particular, we determine whether time series *A* (e.g., IBS) Granger-causes time series *B* (e.g., rapport or a relevant behavior feature) by assessing whether incorporating past observations of time series *A* in a linear regression model of time series *B* and time series *A* reduces prediction error compared to a model containing only previous observations of time series *B*.

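### Mutual smiles, nods and gaze are counted without allowing for chance co-occurrence, so where these counts stand alone individual expressiveness can pass for reciprocity

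*Protocol article*

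**What the plan says.** Section 2 (Background) describes reciprocal instances as those "where both interlocutors engage in the behavior at roughly the same time", or one after another for disclosures. Section 5.3 obtains mutual facial behaviours by software from the individual codes ("Second order behaviors (e.g., mutual smiles) will then be automatically extracted") and treats gaze the same way: "we will then automatically extract the second-order behavior of mutual eye gaze". Table 1 lists reciprocal and non-reciprocal behaviours in parallel rows. The only measure it gives for them is "Number of behaviors per 30 second epoch".

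Chance benchmarks appear in 5.2.2, for IBS: "we will also generate random pairings by calculating IBS with false dyads", followed by "We will also generate a more conservative intra-pair comparison based on temporally shuffled behavior". Nothing comparable is stated for the mutual behaviours.

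Reciprocity is used in these places:
- Section 3: "we predict that we will find stronger and more generalized IBS where conversational behaviors (verbal, non-verbal, and paraverbal) are reciprocal".
- Section 6.2: a mediation analysis with reciprocal behaviours as exposure, rapport as mediator and IBS as outcome.
- Section 6.3 (Claim 3): "whether conversational behaviors Granger-cause IBS or vice-versa", with mutual behaviours named as candidates and 30-second slices as the time unit.
- Section 6.6 (Claim 6): an expectation of more reciprocal behaviour at older ages.
- Section 6.1 (Claim 1): a predictive model that takes both individual and reciprocal behaviours as inputs.

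**The concern.** A mutual smile defined by co-occurrence needs only that both children smile at once. If each smiles often, that happens without either responding to the other. Whatever raises individual smiling, nodding or looking therefore raises the mutual count: age, phase of the session, temperament, a sensitive detector. If the same factor is related to IBS, the mutual count will be related to IBS too.

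The study's argument is that reciprocity, and not mere quantity of behaviour, goes with synchrony. An analysis that uses the mutual count alone cannot tell these apart. The authors accept the principle for the neural measure by comparing real with false dyads. The behavioural side of the same association has no such comparison.

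**Working it through.** The plan states no figure on this point, so there is none to reproduce. From the plan come the 30-second epoch (Table 1), the 176 dyads in four groups of 44 (4.1) and the co-occurrence definition (Section 2). Time-shares, bout length and effect sizes are assumptions, because the article gives no base rates.

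**1. Expected overlap.** For independent children with time-shares pA and pB, expected mutual share = pA × pB. With equal shares p, mutual time per epoch = 30 × p² seconds.

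**2. Expected count.** Assume 3-second bouts on a 0.5-second grid, so each bout ends with probability 0.5/3 = 1/6 per step. Mutual onsets per epoch = 60 × p² × [1 − (5/6)²] = 18.33 × p².

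| Share p, each child | Mutual share | Seconds per epoch | Mutual onsets, formula | Mutual onsets, simulated |
|---|---|---|---|---|
| 10% | 1% | 0.3 | 0.18 | 0.184 |
| 20% | 4% | 1.2 | 0.73 | 0.734 |
| 40% | 16% | 4.8 | 2.93 | 2.939 |
| 60% | 36% | 10.8 | 6.60 | 6.623 |

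From 10% to 20% the simulated count rises by a factor of 0.734/0.184 = 4.0, with no coordination.

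**3. Association with IBS.** 300 simulated studies of 176 independent dyads, one value per dyad, shares drawn from Beta(3,7), IBS correlated 0.5 with the children's summed smiling and with nothing else:

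| Test of reciprocity against IBS | Mean r | Significant at 5% |
|---|---|---|
| Raw mutual count | 0.47 | 100% |
| Mutual share minus pA × pB | 0.00 | 4.7% |
| Raw count adjusted for both children's bout counts | – | 12.3% |
| Raw count adjusted for both children's time-shares | – | 3.3% |

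The Monte Carlo standard error near 5% is √(0.05 × 0.95/300) = 1.3 points. So 3.3% and 4.7% are compatible with 5%, and 12.3% is not. Time-shares are the better adjustment.

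**4. Age pattern.** With 44 independent dyads per group and mean individual smiling rising from 20% to 29% (assumed), chance overlap grows by about (0.29/0.20)² = 2.1. Raw mutual onsets showed a significant age rise in 99.5% of runs, overlap above chance in 6.5%.

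**5. Claim 3.** Granger tests fitted within a dyad (20 epochs, lag 1), with a constant dyad trait raising both smiling and IBS, rejected in 6% of runs. Constant traits go into the intercept. What remains is expressiveness that changes within a session.

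**6. What correction costs.** In a simulation where mutual behaviour truly drove IBS, power was 99% with the raw count, 80% with overlap above chance and 23–48% with adjustment for individual rates. Under other assumptions the first two were 100% and 55%. The excess measure also behaves oddly at high rates: for perfectly overlapping streams it is 0.50 − 0.25 = 0.25 at a 50% share, 0.90 − 0.81 = 0.09 at 90%, and 1 − 1 = 0 at 100%.

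**The case against.** **The article never calls the counts uncorrected, and it condenses.** It gives no window or overlap rule, and the note in Table 1 sits beside the first row of a table flattened by text extraction. The mediation equation and the conditioning series for the Granger tests are not written out. This stands as a caution. But a measure is stated, reading it as covering the reciprocal rows is natural, and a chance comparison is described for IBS only.

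**The shuffled-behaviour sentence in 5.2.2 might be a behavioural benchmark.** It belongs to the IBS section and produces false dyads by randomising epochs. It does not alter the mutual counts.

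**A reader might infer that every reciprocity analysis fails, including Claims 1 and 6.** The article does not support that. Claim 1 also takes individual counts as inputs, with ablation and SHAP, so misattribution there is reduced. The only model in 6.6 has IBS as its outcome and no reciprocal term; the exposure is in any direct test of the age hypothesis about reciprocal behaviour. Mutual self-disclosure, as illustrated in 5.3, is a contingent exchange and is largely unaffected. Prosodic measures are mixed: mutual shifts are probably exposed, while entrainment is about growing similarity.

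**A reader might also infer that the raw counts should be replaced.** Section 2 makes the shared state itself the construct, and step 6 shows that a pure excess measure changes it and loses power. This objection stands and shapes the fix.

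**The simulated regressions are not planned analyses.** That is right. The 100% shows that confounding is possible under stated assumptions. It is not the plan's error rate.

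**Conclusion.** The concern holds in limited form. Mutual smiles, nods and gaze, and probably mutual prosodic shifts, mix coordination with individual rates. Where they stand alone as evidence of a dyadic process, an association can be produced by individual expressiveness. That covers the mediation in 6.2, tests of the Section 3 prediction outside the Claim 1 model, any direct test of more reciprocity with age, and Claim 3 for within-session changes in expressiveness.

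The direction follows from the product rule and is certain. The size depends on base rates, bout lengths and the link between individual behaviour and IBS, none of which the article gives. No stated figure is wrong and the individual streams are kept, so the gap can be closed in analysis. This is a worthwhile correction, not a defect that invalidates the design.

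**What to change.** Keep the mutual counts of Table 1 and add two provisions.

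1. Include both children's individual rates, preferably time-shares, in the mediation of 6.2 and in every other model with a co-occurrence reciprocal term. Use them as conditioning series in the Granger tests of 6.3.
2. Compute the same mutual measures for the false dyads of 5.2.2, or for streams shifted in time within the same phase. Report overlap above chance beside the raw count, including in any comparison across ages.

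Attribute an effect to reciprocity only if it survives these steps. If it does not, report it as not separable from individual expressiveness, since the adjusted test may have low power.

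The cost is a short script on streams already extracted and a few sentences in 5.3, 6.2 and 6.3. The real price is power for the reciprocity-specific effect, because mutual and individual rates are correlated; in step 6 the loss was considerable. Section 4.2 plans to analyse and publish the 9–10-year-old dyads first, so the rule should be fixed before then.

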### 5.4 Rapport estimation

We argue that analyzing only conversational behaviors with respect to IBS without associating them to underlying psychological states obscures how those psychological states are produced dyadically through particular multimodal conversational behaviors. For this reason we will carry out careful objective estimation of the level of rapport between the children in each dyad by using the “thin-slice” method, described above, in which the video is divided into 30-second “thin slice” segments (Ambady and Rosenthal, 1993; Ambady et al., 2000). These segments will be presented in random order to four independent raters on an online micro-work platform (such as Amazon Mechanical Turk or Prolific). The annotators will be provided with a simple one sentence definition of rapport as harmony and ease of interaction, and asked to evaluate each slice of video on a Likert scale ranging from 1 to 7, where higher scores indicate higher rapport (Sinha and Cassell, 2015a). A single rapport value for each slice will be produced by throwing out the rater most distant from the other three, and then calculating intraclass correlation and Cronbach's alpha among the remaining raters to determine consistency and reliability, respectively (Ambady and Rosenthal, 1993; Madaio et al., 2018). The 30-second slices will then be reassembled in their original order, giving a picture of the temporal dynamics of rapport over the course of the interaction.

While we sometimes refer to feeling instantly “in sync” with somebody we have just met, for the most part rapport fundamentally has to do with the change of a relationship over time. In order to assess the changes in rapport over the course of the 6 weeks of the longitudinal experiment, we will rely on the concept of utopy (Sinha, 2016). Prior work has shown that statistical summaries such as a measure of central tendency or proportion of high and low ratings of rapport, collapse the temporal dimension and are not as robust as more stochastic-based models which capture the evolution of rapport over time (Sinha, 2016). We will thus fit a Markov chain of order 1 to the sequence of 16 to 20 rapport ratings for each session (8–10 min), the sequence of 32 to 40 rapport ratings over the two dyadic sessions (collaboration and open-ended chat) and the 192 to 240 rapport ratings for the two dyadic sessions over the entire 6 weeks, and use the resulting transition probability matrix to generate a measure of the “utopy,” or likelihood of the dyad being in a high-rapport state. This likelihood is calculated as the sum of each transition probability weighted by the distance of the transition (Sinha, 2016; Madaio et al., 2017b). This allows us to assess the temporal dynamics of rapport.

As described above, we will also ask children after each interaction to rate their preferred closeness and feelings of closeness to their partner.

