Finally, we will annotate verbal or linguistic behaviors using the Elan software package, version 6.7 (Wittenburg et al., 2006), concentrating specifically on what are called conversational strategies—ways of speaking that serve particular interpersonal functions (such as using praise to “soften up” one's interlocutor, or hedges to avoid embarrassing the other person), that have been shown to play a role in building rapport among adults and young people (Zhao et al., 2014; Madaio et al., 2018). Our coding scheme for conversational strategies, refined and published in numerous papers over the last decade, is based on behavioral phenomena that have been shown in work by others and by our own team to impact rapport. Each coding scheme treats one verbal behavior. In the current work, we will annotate self-disclosure (revealing details about oneself that are not publicly available, such as “I love dogs”), reference to shared-experience (referring to an event that was engaged in together, such as “last week's problem was really hard, right?”), praise (such as “you're better at this than me”), and backchannels (sounds or words that indicate that the listener is following, such as “uh huh” or “yeah”). We will then use a grounded theory (Glaser and Strauss, 1967) bottom-up approach on a subset of the data from each age to understand if we have missed any relevant conversational strategies in the dataset and we will add them to the annotation scheme if so. Following this, we will automatically extract second-order conversational strategies, such as mutual self-disclosure (“I love dogs.” “Me too”). Annotation of conversational strategies will be carried out by experienced annotators whose inter-rater reliability on Krippendorf's alpha must be above 0.7 before they proceed to annotating independently (Krippendorff, 2011). Importantly, we will annotate only what is visible, and then correlate with the underlying dyadic psychological state of rapport, rather than placing annotation of putative underlying states such as beliefs (e.g., this child likes her partner), feelings (she looks happy), and/or intentions (she wants to convince the other child that she's right) on the same level as visible behaviors.

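### Rapport reliability is computed after dropping, apparently slice by slice, the rater who disagrees most, so the reported ICC and Cronbach's alpha are biased upward

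*Protocol article*

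**What the plan says.** Section 5.4 (Rapport estimation) describes the rating: "These segments will be presented in random order to four independent raters on an online micro-work platform". The raters are given a one-sentence definition and "asked to evaluate each slice of video on a Likert scale ranging from 1 to 7".

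The reduction to one number follows: "A single rapport value for each slice will be produced by throwing out the rater most distant from the other three". The same sentence then moves on to "calculating intraclass correlation and Cronbach's alpha among the remaining raters to determine consistency and reliability, respectively". The two steps are joined as "throwing out the rater most distant from the other three, and then calculating intraclass correlation", so the order is fixed: discard first, assess agreement second, and only on the three who remain. The section does not say how those three ratings are combined.

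Section 2 (Background) explains why this score matters: "it is essential to require ground truth as to the strength of the psychological state of rapport". The score enters the time-warping and mediation analyses (6.2), the Granger tests (6.3), the utopy score and quadratic regression (5.4, 6.4) and the six-week analysis (6.5).

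**The concern.** A reliability coefficient is meant to show whether raters agree because they see the same thing. If the least agreeing of four ratings is removed first, the remaining three are closer together whatever the true reliability is. Within-slice variance falls because the largest deviation has gone. Between-slice variance rises because the mean of the three survivors moves away from the removed value. Both changes push ICC and alpha up.

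The raters are untrained and work online, so their true reliability is uncertain and worth measuring without bias. Measurement error in rapport weakens its associations with inter-brain synchrony and tends to flatten a quadratic curve. With flattering coefficients in the report, a null result for Claim 2 or Claim 4 could be read as substantive when the ratings were simply poor.

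**Working it through.** The article states no reliability figure for rapport, so there is nothing to reproduce. The check simulates the stated rule.

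**Inputs from the article.** Four raters, a 1 to 7 scale, the most distant rater dropped, and ICC and alpha on the other three (all 5.4). For small samples, "the sequence of 32 to 40 rapport ratings over the two dyadic sessions" gives 32 to 40 slices per weekly pair of sessions (5.4).

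**Assumptions not in the article.** Latent normal scores with SD 1.4, rounded to 1 to 7. The rater furthest from the mean of the other three is dropped, with ties broken at random. The retained ratings are averaged into the slice score.

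**Formulas.** With k raters, ICC(1,1) = (MSB − MSW) / (MSB + (k − 1)·MSW). For exchangeable raters, alpha = k·ICC / (1 + (k − 1)·ICC).

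**Step 1: reliability, per-slice discard.**

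| True agreement | ICC, all four | alpha, all four | ICC, after discard | alpha, after discard |
|---|---|---|---|---|
| None | 0.00 | 0.00 | 0.46 | 0.72 |
| Single-rater ICC about 0.29 | 0.29 | 0.62 | 0.66 | 0.85 |

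The alphas agree with the formula:
- noise after discard: 3 × 0.46 / (1 + 2 × 0.46) = 1.38 / 1.92 = 0.72
- real agreement, all four: 4 × 0.29 / (1 + 3 × 0.29) = 1.16 / 1.87 = 0.62
- real agreement after discard: 3 × 0.66 / (1 + 2 × 0.66) = 1.98 / 2.32 = 0.85

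The result is not sensitive to the noise model. Uniform 1 to 7 noise gives ICC 0.53 and alpha 0.77 after the discard. Using summed pairwise distances to pick the dropped rater changes the results by no more than 0.001. Three raters chosen at random from noise give about 0, so the inflation comes from the selection and not from having three raters.

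**Step 2: the other reading.** If one whole rater is dropped per session, pure noise reaches an ICC of only about 0.02 to 0.09, depending on the number of slices. A single-rater ICC of 0.28 becomes about 0.35 to 0.36 with 16 to 20 slices.

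**Step 3: accuracy of the slice score, similar raters.** At a single-rater ICC of about 0.29, the correlation with true rapport is about 0.78 for the mean of four, 0.75 for the median and 0.70 after the discard. With normal errors, total variance 1 and ICC 0.30, the error variance is 0.70. The mean squared error (MSE) is then 0.70 / 4 = 0.175 for four raters and 0.70 / 3 = 0.233 for three random raters. After the discard it is 0.308 by simulation, and 0.308 / 0.175 = 1.76. The rule therefore does worse than losing a rater at random.

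**Step 4: accuracy with careless ratings (uniform 1 to 7), MSE.**

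| Attentive-rater ICC | Careless share | Mean of four | After discard | Median of four |
|---|---|---|---|---|
| 0.5 | 10% | 0.401 | 0.612 | 0.451 |
| 0.7 | 10% | 0.328 | 0.399 | 0.314 |
| 0.9 | 10% | 0.258 | 0.198 | 0.179 |
| 0.9 | 20% | 0.455 | 0.332 | 0.302 |

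At ICC 0.9 with 10% or 20% careless ratings the discard beats the mean. At ICC 0.7 or lower the mean had the smaller MSE at every careless share tried (5% to 50%), although squared correlation sometimes favoured the discard slightly (0.707 against 0.693 at ICC 0.7 and 20%). The median had a smaller MSE than the discard in every scenario tried.

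**The case against.** **The unit of the discard is not certain.** The sentence drops a rater rather than a rating, and alpha is normally computed on a fixed set of raters across slices. That fits the removal of one whole rater, under which the inflation is small. This stands as a condition on the size. The per-slice reading is still the more natural one, because the discard is how the value for each slice is said to be produced.

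**Chance-level ratings would not pass everything.** A reader might infer that pure noise would clear any usual reliability threshold. The figures do not support that. In sets of 40 noise slices, ICC after the discard is below 0.7 in essentially every set and below 0.5 in about 65%. Alpha is below 0.7 in about 40% of sets of 40 and about 23% of sets of 240. Noise therefore fails on ICC and only borders on 0.7 for alpha. Nor does the article set a minimum for rapport. Its 0.7 rule ("inter-rater reliability on Krippendorf's alpha must be above 0.7 before they proceed to annotating independently", 5.3) concerns verbal coding and a different coefficient.

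**Discarding an outlier can help.** A reader might also infer that the discard always gives a worse score. It does not. Careless responding is a plausible worry on a micro-work platform, and step 4 shows the discard beating the mean when attentive raters agree very closely. This stands as a limit on the accuracy point. It does not rescue the reliability figures, which are inflated in either case.

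**Precedent, condensation and use.** The article cites earlier work for the procedure, and a fuller protocol may contain attention checks, thresholds or all-rater coefficients. Their absence here is not held against the plan. No planned test uses the ICC or alpha. But the order of discard and measurement is stated outright, and neither precedent nor an unseen document removes the bias from it.

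**Conclusion.** The concern holds in a limited form. The stated procedure selects on agreement and then measures agreement, so the reported ICC and alpha will be too high.

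On the per-slice reading the bias is large: about 0 becomes 0.46 (ICC) and 0.72 (alpha), and a modest single-rater ICC of 0.29 is reported as 0.66. On the whole-rater reading it is small. The sizes rest on simulated errors, but normal, rounded and uniform noise give similar results.

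The loss of accuracy in the slice score is conditional. It assumes that the three retained ratings are averaged, and it applies when rater errors are similar or agreement is low to moderate.

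The effect on the trial is indirect. The planned tests remain as they are, but readers would be misled about the quality of the measure that the article treats as its reference for rapport.

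**What to change.** In section 5.4:

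- Compute and report ICC (single-rater and four-rater average) and Cronbach's alpha on all four raters, before any exclusion.
- Score each slice by the mean of the four ratings, or by the median if careless crowd raters are a concern, and state which.
- Exclude raters only on pre-specified criteria that do not depend on agreement within the slice, such as failed attention checks.
- Keep the discard as a sensitivity analysis, saying whether it works per slice or per rater and how the remaining ratings are combined.

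All four ratings are collected anyway, so no new data are needed and the change is a short edit. The cost is a reported reliability that looks less favourable.
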